### Selection of Subjects

Subjects of both genders will be recruited in two centers: the Multiple Sclerosis Center of the Sapienza University of Rome and the Multiple Sclerosis Center of the IRCCS Regina Elena National Cancer Institute. The planned recruitment period will be of three years.

Prior to enrollment, all participants will be screened to check their inclusion and exclusion criteria.

Patient inclusion criteria will be:

Patients diagnosed with relapsing-remitting MS (93)Patients untreated or treated with only immunomodulatory therapy18–60 years old

Patient exclusion criteria will be:

pregnancyco-existing neoplastic, hematologic, thyroid, metabolic, thrombotic, or autoimmune diseasesdrug or alcohol addictedtherapy with immunosuppressive drugs, steroids, or any medication interfering with coagulation

We will evaluate 3 groups of subjects: 30 RRMS patients in relapse (Group I); 30 RRMS patients in remission, i.e., without relapse in the previous 2 months (Group II), and 30 sex- and age-matched healthy controls (Group III).

A relapse or exacerbation or “attack” was defined by the multiple sclerosis guidelines as a manifestation of new or worsened neurological symptoms lasting for more than 24 hours (94). Symptoms should be supported by subjective description and by objective clinical assessment with no other explanation for them. The relapse is separated from the previous “attack” by at least 30 days and usually persists for days or weeks, then slowly improves over weeks or a few months ending with partial or complete recovery, i.e., remission. MRI showed the new and/or active lesions in the majority of patients, and steroid therapy often accelerates the recovery of symptoms.

Relapse needs to be distinguished from a pseudo-exacerbation, which is defined as a temporary worsening of pre-existing symptoms without new MS-related neuroinflammation, thus an MRI does not detect active or new lesions (95). The causes of pseudo-relapses could be different and include infections with or without fever, increased body temperature due to over-exercising, sauna, hot shower/bath or weather, dehydration, hormonal changes during menstruation or severe psychological stress, surgery, trauma, medications, alcohol overuse, and several medical conditions as thyroid or other metabolic disorders. Pseudo-relapses usually last less than 24 hours and resolve after removing their triggering causes with no need for steroid therapy.

We will only include MS patients in relapse who have new symptoms for more than a day but no more than a month and possibly as soon as they communicate the neurological symptoms to their doctor to quickly perform all protocol procedures before starting treatment with steroids. Patients in relapse already on steroid therapy cannot be enrolled in the study. This includes both naïve and treated patients as they could raise some concerns regarding the possibility that treatment could affect levels of some of the biomarkers studied. Indeed, it would be ideal to recruit only untreated patients, although it should be taken into account that other concomitant factors (lifestyle, nutrition, current infections, physical activity, smoking, etc.) could influence these biomarkers, albeit to a lesser extent. The choice to include patients on immunomodulating (but not immunosuppressive) therapy was dictated by the actual difficulty in finding untreated patients out of those just diagnosed. However, since the two compared groups of patients, i.e., in relapse and in remission, are recruited from the same outpatient population, the treatment influence could be sufficiently balanced between these groups and, in any case, it will be weighed in the final analysis.

An informed written consent will be obtained by all participants. The study information will be provided to the patients by the investigator to explain the study aims and protocol procedures, risks, and benefits (96). We will encourage the patients to take time before signing the consent form to discuss their participation in the study with their trusted advisors. We want to highlight that the timing of our study procedures largely coincides with the routine clinical MS management. In fact, relapsing patients usually perform blood sampling to evaluate the general clinical status and Gd-enhanced MRIs to define the extent of radiological disease activity. Regarding remitting MS patients, study participation will be proposed only to patients who need to perform their routine periodic blood tests or neuroimaging. A greater amount of blood required for additional laboratory tests pre-specified in the study and perfusion sequences, both of them with their relative low risk, merely represent the only difference between study procedures and equivalent routine exams. The benefits of participating in the study could consist of more rapid MRI execution not always easily accessible in routine practice.

On the other hand, healthy people, potentially research subjects, will have only blood sample collection for the pre-specified laboratory assessment; they will not undergo Gd-enhanced MRIs since it represents, in any case, a reasonable low risk related to the use of contrast. Patients will be seen and assessed for physical disabilities using the Expanded Disability Status Scale (EDSS) (97) and Multiple Sclerosis Functional Composite (MSFC) (98).

Each subject included in the study will remain anonymous for privacy reasons and identified by a progressive numeric code (ID number) (associated with their own name, surname, and date of birth in a separate database) so that all serum/plasma samples and MRI data will be treated and processed blindly. An ad-hoc secure database has been established to collect standardized data from different centers, data storage, and sensitive data protection.

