### Data Analysis

#### Sample Size Calculation

Overall 90 subjects (30 for each group) will be enrolled to compare the level of complement C4a (55). By using the ANOVA test, this sample size will allow detection of effect size values [delta=(miA–miB)/sigma] equal to at least 0.71, with a statistical power of 80%, to a level of significance of 5%.

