#### Statistical Methods

Descriptive statistics will be used to summarize pertinent study information. Correlations between quantitative variables will be assessed with the Pearson r correlation. The associations will be analyzed by the Fisher exact test or Chi Square test for trends. Comparisons between disease subgroups and control group will be carried out for different variables, using either Student’s *t-*test or analysis of variance (ANOVA). If the ANOVA shows a statistical difference between subgroups, a post-hoc analysis with Bonferroni correction for multiple comparisons will be performed. For non-normally distributed data, non-parametric (Mann Whitney-U or Kruskal-Wallis-H) tests will be used. The level of significance is set at p ≤ 0.05 (SPSS version 20.0, SPSS Inc., Chicago, Illinois, USA).

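### Three non-randomised groups are recruited at two centres with no balance by centre, and the named tests carry no centre term, so group comparisons are open to confounding by centre

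*Protocol article*

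**What the plan says.** All references are to the protocol article. Selection of Subjects states that subjects will be "recruited in two centers: the Multiple Sclerosis Center of the Sapienza University of Rome" and a second multiple sclerosis centre at a cancer institute. It defines the groups as 30 patients in relapse, 30 in remission and 30 healthy controls matched on sex and age. No ratio of groups per centre is set, and centre is not a matching variable.

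The same section discusses whether immunomodulatory treatment could distort the relapse-remission comparison. It answers that the two patient groups "are recruited from the same outpatient population, the treatment influence could be sufficiently balanced between these groups" and adds that treatment will be taken into account in the final analysis.

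Statistical Methods says "Comparisons between disease subgroups and control group will be carried out for different variables", by t-test or ANOVA with Bonferroni post hoc tests, or by Mann-Whitney or Kruskal-Wallis. The abstract names ANOVA and unpaired t-tests. Centre appears in none of these. It is also absent from the features that the additional secondary outcomes relate to laboratory and MRI findings (age, gender, disability, disease duration).

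**The concern.** Group membership follows from who presents where, not from randomisation. Relapse patients enter when they report symptoms. Remission patients enter when they are due for routine tests or imaging. How controls are divided between the centres is not described. Nothing keeps the three groups in similar proportions at each centre.

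Centre can carry case mix, clinic routine and pre-analytical handling; Blood Processing allows up to 3 hours between collection and separation. If one centre's values run higher and it supplies more of one group, an unadjusted comparison attributes that difference to relapse or to disease. At stake are the primary laboratory comparisons, which involve the controls, and the relapse-remission perfusion comparison.

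**Working it through.** **The plan's own figure.** Sample Size Calculation enrols 30 per group for C4a and gives a detectable standardised difference "equal to at least 0.71" at 80% power and 5% significance, by ANOVA. Taking one group to differ by δ and the other two to be equal, the noncentrality is 30 × (2/3) × δ². At δ = 0.71 this is 20 × 0.5041 = 10.08. With 2 and 87 degrees of freedom, power is 80.4% and the detectable δ is 0.706. The figure reproduces. A single two-group t-test (58 df) has 77.2% power at 0.71, which is the reference for the pairwise results below.

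**Inputs not in the documents (assumptions).**
- Numbers from one centre in the two compared groups: 15/15, 18/12, 20/10 or 24/6, each out of 30.
- Centre shift s in the marker: 0.25, 0.5 or 1.0 SD, with SD taken within centre and group.

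**Bias if centre is ignored.** Bias = s × (k1 − k2)/30. For s = 0.5:
- 15/15: 0.5 × 0/30 = 0
- 18/12: 0.5 × 6/30 = 0.10 SD
- 20/10: 0.5 × 10/30 = 0.167 SD
- 24/6: 0.5 × 18/30 = 0.30 SD

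**False-positive rate of the two-group t-test at nominal 5%** (40,000 simulated trials per cell, no true group difference):

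| Centre shift | 15/15 | 18/12 | 20/10 | 24/6 |
|---|---|---|---|---|
| 0.25 SD | 4.7% | 5.3% | 6.0% | 8.3% |
| 0.5 SD | 4.2% | 5.9% | 8.8% | 19.5% |
| 1.0 SD | 2.9% | 7.8% | 18.2% | 56.6% |

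Hand check of 24/6 at 0.5 SD:
- The estimated variance is about 1 + 0.25 × 0.8 × 0.2 × 30/29 = 1.041, so the estimated standard error is √(2 × 1.041/30) = 0.263.
- The rejection limit is 2.00 × 0.263 = 0.527.
- The true standard error is √(2/30) = 0.258, and (0.527 − 0.30)/0.258 = 0.88, an upper-tail probability of about 19%. This agrees with the simulation.

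For the three-group ANOVA with the third group at 15/15 and s = 0.5, the rates are 5.2% (18/12), 7.0% (20/10) and 14.6% (24/6).

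**With centre in the model (57 df).** Even at a 1.0 SD shift the false-positive rate is 5.1% (15/15), 5.1% (20/10) and 4.8% (24/6). The standard error of the group difference is √(2/30)/√(1 − r²), with r = (k1 − k2)/30:
- 15/15: r = 0, SE 0.258, power for 0.71 is 77.1%
- 20/10: r = 1/3, SE 0.274, power 72.2%
- 24/6: r = 0.6, SE 0.323, power 58.0%

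**The case against.** **The article is condensed.** A centre covariate is the kind of detail a full analysis plan may hold. Statistical Methods is plainly not exhaustive, since it names no model for the treatment influence that Selection of Subjects promises to consider. This stands in part: one can say only that the tests as named do not account for centre. It does not reach recruitment. Balance by centre is settled at enrolment, and Selection of Subjects does state what controls are matched on.

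**A reader might infer that the source-population argument contradicts the two-centre design.** It does not. Both patient groups can come from the pooled outpatients of the same two clinics. The remark that they "are recruited from the same outpatient population" is about treatment influence in those two groups. It makes no claim about centre, and it neither establishes balance by centre nor covers controls.

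**A reader might infer that an uneven mix alone produces a false difference.** It does not. Levels must also differ by centre, and the article gives no evidence that they do. Several provisions make large shifts less likely: one blood-processing procedure, a named analyser or kit for most assays, a single set of MRI parameters with joint reading by two radiologists, blinded processing and a standardised database. These do not remove differences in case mix or in handling time within the 3-hour limit. A second scanner is conjecture, and so is any inference from one site being a cancer institute: that site is also an MS centre, and co-existing neoplastic disease is a patient exclusion.

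**Milder inputs do little harm.** This is true: at 18/12 and 0.5 SD the rate is 5.9%, and with an even split the test is slightly conservative.

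**Conclusion.** The point holds as a conditional weakness of design and analysis. As described, nothing prevents an uneven group mix between centres, and the named tests would not correct for one. The harm runs from none (even split, or no centre shift) through modest (about 9% false positives at 20/10 and 0.5 SD) to serious (19–20% at 24/6 and 0.5 SD, where the spurious 0.30 SD is over two fifths of the design difference of 0.71). All of these sizes rest on assumed splits and shifts. The documents do not show that confounding by centre will occur, only that the comparisons are not protected against it.

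**What to change.** 1. **Selection of Subjects:** match controls to patients on centre as well as sex and age, and aim for a similar relapse-to-remission ratio at each centre as far as feasible.
2. **Statistical Methods:** include centre as a fixed factor in the group comparisons, with a van Elteren or other stratified rank test as the non-parametric version. Report group counts by centre.
3. The remark on the shared outpatient source can stay as an argument about treatment, but should not be relied on for balance by centre.

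**Cost.** When groups are balanced by centre, adjustment costs one degree of freedom and almost no power (77.1% against 77.2%). When they are not, it costs real power, as the working shows, so balancing recruitment is preferable to relying on adjustment alone. Keeping the ratio similar may slow enrolment, because relapse patients must be caught within a month of onset and before steroids; hence a target rather than a strict quota.

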**Primary outcomes:**

To evaluate serum/plasma concentrations of complement (C3, C4, C4a, and C9), Fibrinogen, Factor VIII (FVIII), Factor X (FX), D-dimer (DD), PC, PS in relapsing-remitting MS (RRMS) patients and healthy people.

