**Additional secondary outcomes:**

To assess relative CBF, CBV, and MTT by DSC 3.0-T MRI in relapsing MS patients compared to remitting MS patients.To evaluate number and volume of enhancing lesions in relapsing MS patients compared to remitting MS patients.To evaluate the relationships between laboratory data, demographic/clinical (age, gender, disability and disease duration) features, and MRI perfusion findings in the patients’ groups.

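### Smoking, nutrition and physical activity are named as influences on the biomarkers, but healthy controls are matched on sex and age only and compared without stated adjustment, leaving the RRMS-versus-healthy primary contrasts open to lifestyle confounding

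*Protocol article*

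**What the plan says.** All references are to the protocol article.

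- **Named influences.** Selection of Subjects, in discussing treated and untreated patients, says that "other concomitant factors (lifestyle, nutrition, current infections, physical activity, smoking, etc.) could influence these biomarkers, albeit to a lesser extent". The comparison is with treatment, and no figure supports the ranking.
- **Balance argument.** The same paragraph expects that "the treatment influence could be sufficiently balanced between these groups and, in any case, it will be weighed in the final analysis". The reason it gives is a common source: "since the two compared groups of patients, i.e., in relapse and in remission, are recruited from the same outpatient population". The argument is about treatment, and about Groups I and II.
- **Controls.** The third group is "30 sex- and age-matched healthy controls (Group III"). The eligibility lists are worded for patients ("Patient exclusion criteria will be" heads the second), and smoking, diet and activity are not among the criteria.
- **Primary outcomes.** Ten complement and coagulation markers, C3 through protein S, are to be evaluated "in relapsing-remitting MS (RRMS) patients and healthy people".
- **Analysis.** Statistical Methods names Student's t-test or ANOVA, Bonferroni post-hoc comparisons after a significant ANOVA, and Mann-Whitney or Kruskal-Wallis tests for non-normal data. It states no covariate for the comparison of patients with controls.

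**The concern.** The protocol identifies factors that can move its own markers and then, in the text shown, neither matches, restricts nor adjusts for smoking, nutrition or activity when patients are compared with healthy people. Two of the three group pairs involve Group III. If smoking is more or less common among patients than among the controls, part of any difference in fibrinogen, FVIII, D-dimer or complement could come from smoking. It would be read as coagulation or complement activation in MS, which is the study's hypothesis. A larger sample does not shrink such a bias. It can be handled in the analysis only if the variable was recorded.

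Current infections, in the same list, are a different matter: viral serology is a key secondary outcome in patients and healthy people, and a PCR panel is described.

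**Working it through.** **1. The plan's own figure.** Sample Size Calculation gives 30 per group, ANOVA, 5% significance, 80% power and a detectable difference of 0.71 SD. For group means (0, 0, 0.71) the noncentrality is

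λ = n × Σ(mean − grand mean)² = 30 × (2/3) × 0.71² = 10.08.

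With 2 and 87 degrees of freedom the power is 80.4%, so the figure reproduces. The sample size is not in dispute.

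**2. Which group pairs the balance argument reaches.**

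| Pair | Treatment balance argued | Lifestyle balance argued | Matching stated |
|---|---|---|---|
| Relapse v remission | yes | no | none |
| Relapse v healthy | no | no | sex, age |
| Remission v healthy | no | no | sex, age |

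The shared outpatient source makes a lifestyle difference between the first pair less likely, even though the protocol does not argue this. It does nothing for the other two pairs.

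**3. Size, on assumed inputs.** The documents give neither smoking prevalences nor effects on any marker. For one yes/no factor,

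bias (in SD) = difference in prevalence × effect of the factor (in SD).

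| Assumed prevalence difference | Assumed effect | Bias | Share of 0.71 SD |
|---|---|---|---|
| 10 points | 0.3 SD | 0.03 SD | 4% |
| 20 points | 0.5 SD | 0.10 SD | 14% |
| 30 points | 0.8 SD | 0.24 SD | 34% |

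**4. False-positive rates per marker.** Assume no true difference and the same bias b in both patient groups. Then λ = 30 × (2/3) × b² = 20b².

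- b = 0.03: λ = 0.018
- b = 0.10: λ = 0.20
- b = 0.24: λ = 1.152

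| Bias | Three-group ANOVA | Given patient-control pair, after ANOVA and Bonferroni | Simple t-test, 30 v 30 |
|---|---|---|---|
| 0.03 SD | 5.1% | 1.7% | 5.1% |
| 0.10 SD | 6.5% | 2.4% | 6.7% |
| 0.24 SD | 14.3% | 6.8% | 15.0% |

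The ANOVA and t-test columns come from the noncentral F and t distributions. The pairwise column was simulated (one million replicates). With no bias it is 1.6%, so 6.8% is about a fourfold rise from a low base.

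**5. Cost in degrees of freedom.** The planned ANOVA leaves 90 − 3 = 87. Adding age, sex and smoking leaves 84; adding body-mass index as well leaves 83.

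**The case against.** The strongest reply is that this is a condensed article. Form items and covariate lists usually sit in a full protocol or analysis plan, neither of which is shown, and the study database is mentioned without its contents. That stands in part. A reader might infer that smoking will not be recorded, especially as healthy people are said to have only blood sampling. But that remark contrasts them with patients who also have MRI; it is not a list of data fields. What the article does fix is the matching on sex and age and the type of test.

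Three other stronger readings also fail.

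- A reader might infer that the protocol relies on the shared outpatient source to balance lifestyle and wrongly stretches this to controls. The sentence concerns treatment and is already confined to the two patient groups, so it needs no correction. For lifestyle there is simply no balancing argument.
- The phrase "demographic/clinical (age, gender, disability and disease duration) features" might be taken as the covariate list for the primary comparison. It belongs to an additional secondary aim on relationships within the patient groups.
- Body weight might be added as a second confounder. The protocol does not name it, so it carries no weight here.

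It is also fair to say that Group II is an internal comparator. A lifestyle difference between MS patients and healthy people would tend to shift Groups I and II alike, and so would not by itself create a relapse-remission difference. The working hypothesis about relapse is therefore less exposed than the primary outcomes as worded.

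**Conclusion.** The concern holds in limited form. On the protocol's own account, lifestyle factors can shift the markers, and nothing stated protects the RRMS-versus-healthy primary contrasts against smoking, nutrition or activity. This is a common limitation of a small comparison with healthy controls, and recording one variable reduces it at little cost. It is not a contradiction in the plan.

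Its size is unknown. The range of about 5% to 14% for the three-group ANOVA (about 2% to 7% for a given pair after Bonferroni) rests wholly on an assumed bias of 0.03 to 0.24 SD, equal in both patient groups. At the low end the effect is negligible. At the high end the bias is about a third of the difference the study is sized to detect, and the exposure applies to each of the ten primary markers.

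**What to change.** Record current smoking (yes/no) for all 90 subjects at enrollment, unless the full protocol already does so. Body-mass index is optional.

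For each primary marker, compare patients with controls by a linear model containing group, age, sex and smoking, and report it beside the planned unadjusted test. For non-normal markers, fit the model on a transformed or rank scale, in keeping with the rank tests already planned.

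The cost is one enrollment item and three of 87 residual degrees of freedom (four with body-mass index). Matching controls on smoking as well is optional and would make their selection slightly harder. The treatment-balance sentence can stay as it is. Nutrition and physical activity would remain unadjusted and should be named as a limitation when the patient-control results are interpreted.

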### Interventional Methods

#### Laboratory Procedures

At enrollment, blood samples will be obtained from each participant. For most laboratory markers that will be investigated in this study (e.g., blood count test, coagulation factors, complement components, anti-cardiolipin antibody, anti-β2 glycoprotein I antibody, anti-prothrombin IgG/IgM and anti-AnnexinV IgG/IgM, RNA extraction, and Real Time polymerase chain reaction) technical procedures are already well established and are a part of the clinical laboratory practice. In regards to the technical procedures, we will use other specific molecular markers for measuring (i.e., angiopoietin-1, angiopoietin-2, FIII/TF, Tie-2, VEGF). We will refer to the available literature data and evidence.

